### Data Analyses

Data will be analyzed according to the intention-to-treat principle (ITT). To address missing data for the ITT analyses, we will apply multiple imputation procedures with the package Amelia in R (R Foundation for Statistical Computing, Vienna). Amelia uses a bootstrapping-based algorithm that gives essentially the same answers as the standard imputation posterior or expectation maximum approaches according to the authors. We plan to use between 20 and 40 imputed datasets depending on the amount of missing data according to suggestions by Graham [46]. The imputation model will include all primary and secondary outcome variables. Auxiliary variables such as demographic data may be included if they improve convergence of the imputation model.

Differences between study arms in primary and secondary continuous outcome variables at baseline and the follow-up points will be tested using linear mixed models (LMM). LMMs will be specified appropriately to model clusters and repeated measures by defining random effects for study arms and time (repeated measures). For nonnormal continuous outcomes, appropriate distributions (eg, negative binomial and zero-inflated) will be specified. For binary outcomes, a generalized linear mixed model (GLMM) will be specified that defines an appropriate link-function. In the GLMM fixed effect, coefficients will be interpreted in the context of the subject-specific (nonmarginal) model fit.

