### Measurements

Table 4 provides an overview of measurements. Sociodemographic data will include subject gender, age, and level of education.

The primary outcome of interest will be the number of days of cannabis use on the preceding 7 days according to the Time-Line-Follow-Back method [35,36].

Secondary outcomes of interest will include the quantity of cannabis used in the previous week, in standardized cannabis joints (as indicated in the consumption diary as well, as per Schaub et al [10]). Participants can choose between three different cannabis forms presented in photographs and in the second step between five different standard joints for each category (1/10 g, 1/6 g, 1/4 g, 1/3 g, and 1/2 g content pictures). These joints are either pure cannabis or cannabis mixed with tobacco. Finally, every participant has his or her personal standard tobacco cigarette, a ruler with centimeter and millimeter scales, the fraction amount in grams, and an open 10 cm paper prepared to roll a joint and containing the cannabis plant- or resin-tobacco mixture or pure cannabis presented in his or her consumption diary. Further secondary outcomes are the presence and severity of a cannabis use disorder (Cannabis Use Disorder Identification Test-Revised, CUDIT-R); the severity of cannabis dependence (Severity of Dependence Scale, SDS); the use of alcohol, tobacco, or other illicit drugs besides cannabis (Fragebogen Substanzanamnese, FDA); changes in depression, anxiety, and attention deficit symptoms (Center for Epidemiologic Studies Depression Scale, CES-D; general anxiety disorder-7, GAD-7; and Adult ADHD Self-Report Scale-V1.1, ASRS-V1.1); the Short Screening Scale for Diagnostic and Statistical Manual of Mental Disorders, 4th edition (DSM-IV) posttraumatic stress disorder (PTSD); client satisfaction (Client Satisfaction Questionnaire adapted to Internet-based interventions, CSQ-I); and treatment adherence. The perceived relationship between the user and the eCoach will be assessed at the end of the program using the Working Alliance Inventory [37] adapted for Web-based interventions (WAI-TECH).

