### Sample Size Calculation

Anticipating that a Cohen *d* of 0.30 based on our previous study experiences will be realistic for the effect size differences between the unenhanced version of the Web-based tool and the adherence-focused guidance-enhanced version, a sample size of n=176 in each study group would have 80% power to detect this difference based on calculations performed with G*Power software (Faul, Kiel) with an alpha error of 5% and two-tailed testing. Thus, we aim to recruit a total of 528 participants.

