### Limitations

The following protocol limitations must be considered:

First, cannabis users who are currently receiving other treatments to reduce their cannabis consumption will be excluded. However, CANreduce was designed to access cannabis users who—for personal or practical reasons—would not attend traditional addiction counseling. Second, all measurements will be self-reported. Third, most of the self-report instruments we will be using have not been validated in a Web-based context, though they have largely been validated in other research and clinical settings. Fourth, as found in the previous Web-based intervention [10,22], we expect rather high rates of dropouts. Finally, another possible limitation of Web-based studies is the potential for low adherence rate because of the distant nature of intervention.

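### The stated imputation variables do not name the randomised arm and take in program measures that TAU cannot have; followed as written, the arm contrasts shrink towards zero

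*Protocol article*

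**What the plan says.** The Data Analyses section of the protocol article handles missing data for the intention-to-treat analysis as follows: "we will apply multiple imputation procedures with the package Amelia in R". It sets the number of datasets ("We plan to use between 20 and 40 imputed datasets depending on the amount of missing data") and then the content of the model: "The imputation model will include all primary and secondary outcome variables". One further class of variable is optional: "Auxiliary variables such as demographic data may be included if they improve convergence of the imputation model". Study arm is mentioned in neither sentence.

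The next paragraph of the section gives the purpose of the imputed data: "Differences between study arms in primary and secondary continuous outcome variables at baseline and the follow-up points will be tested using linear mixed models (LMM"). The Measurements section counts among the secondary outcomes "client satisfaction (Client Satisfaction Questionnaire adapted to Internet-based interventions, CSQ-I); and treatment adherence". Table 4 places both at week 6 only. Under Randomization and Trial Flow and under Control Conditions, TAU participants are offered the program only once their 3 months are over. On dropout, the Limitations section says "we expect rather high rates of dropouts" and gives no rate.

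**The concern.** An imputation model should contain every term whose effect the analysis will estimate. Here that term is study arm. If arm is absent, missing days of use are drawn from a relation pooled over the three arms. The imputed participants then carry little or none of the arm difference, and the combined contrast is pulled towards zero. The three effectiveness hypotheses are all contrasts between arms, and the sample size is set at 80% power with no stated allowance for dropout, so nothing is in reserve to absorb such a loss.

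The second problem lies in what the list does name. Taken literally, all secondary outcomes include satisfaction with, and adherence to, a program that one third of the sample has not been given. Satisfaction has no observed value in TAU. Adding a TAU indicator to the model does not cure this, because the relation between that indicator and satisfaction cannot be estimated. The two parts therefore have to be corrected together.

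**Working it through.** **Inputs from the protocol article.** Difference of 0.30 SD ("Anticipating that a Cohen *d* of 0.30 based on our previous study experiences will be realistic"), 176 per arm, two-sided alpha 5%, power 80%, total 528, allocation 1:1:1 (Sample Size Calculation; Randomization and Trial Flow).

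**Assumptions, because the article gives no figure.** Correlation 0.5 between any two of baseline, 6 weeks (t1) and 3 months (t2); difference of 0.30 SD at both follow-ups; missing share *m* of 20% to 60%; data missing completely at random in the calculations, a special case of missing at random.

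**1. The plan's own figure.** Normal approximation: n = 2 × (1.960 + 0.842)² / 0.30² = 174.5, so 175 per arm. The noncentral t calculation gives 176 (power 80.1%), and 3 × 176 = 528. The sample size reproduces and is not in dispute.

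**2. Arm omitted, t1 and t2 both missing.** Only baseline is left as a predictor, and it carries no arm difference. The contrast is 0.30 × (1 − *m*):
- *m* = 20%: 0.24
- *m* = one third: 0.20
- *m* = 50%: 0.15

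**3. Arm omitted, only t2 missing.** Pooled over two equal arms, the variance of t1 is 1 + 0.30²/4 = 1.0225 and its covariance with t2 is 0.5 + 0.0225 = 0.5225. In the regression of t2 on baseline and t1, the coefficient of t1 is (0.5225 − 0.5 × 0.5) / (1.0225 − 0.5²) = 0.2725 / 0.7725 = 0.353. Imputed participants carry a difference of 0.353 × 0.30 = 0.106. The contrast is 0.30 × (1 − *m*) + 0.106 × *m*:
- *m* = 20%: 0.261
- *m* = one third: 0.235
- *m* = 50%: 0.203

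**4. Large-sample simulation between these two cases.** It gives 0.24-0.26, 0.20-0.23 and 0.15-0.21 at 20%, one third and 50% missing, in agreement with steps 2 and 3 to within about 0.01. With arm included the contrast is about 0.30 throughout.

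**5. Simulation at the trial's size.** Two arms of 176, bootstrap-based normal imputation, 20 datasets, Rubin's rules, unadjusted comparison at t2, 300 replicates:

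| Missing | Pattern | Estimate, arm in | Estimate, arm out | Power, arm in | Power, arm out |
|---|---|---|---|---|---|
| 20% | t1 and t2 | 0.297 | 0.235 | 70% | 53% |
| 40% | t1 and t2 | 0.298 | 0.184 | 63% | 27% |
| 60% | t1 and t2 | 0.289 | 0.124 | 44% | 5% |
| 20% | t2 only | 0.304 | 0.265 | 73% | 67% |
| 40% | t2 only | 0.305 | 0.218 | 65% | 41% |
| 60% | t2 only | 0.296 | 0.175 | 46% | 17% |

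The fall below 80% in the arm-in columns is the ordinary cost of dropout. Only the gap between arm in and arm out belongs to this point.

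**6. Adherence as a stand-in for arm.** If adherence is in the model and is recorded as zero modules in TAU (assumed uniform on 0 to 8 modules in the active arms), it separates active from TAU in part. Where half to all of those missing t2 also miss t1, the active-versus-TAU contrast is then about 0.27, 0.24-0.25 and 0.22-0.23 at 20%, one third and 50% missing. Without adherence, the same setting gives 0.24-0.25, 0.20-0.22 and 0.15-0.18.

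**The case against.** The strongest reply is that the article never says arm is left out. It says what the model will include, not what it consists of, and the auxiliary sentence is open-ended. A journal article condenses a fuller protocol or analysis plan that is not shown, and a complete imputation specification is commonly left there. This stands as far as it goes. A reader might infer that the model is built from outcomes alone and that arm is excluded; the documents do not support that, since demographics may be added and arm is simply not named. What remains is that the article does more than name a method. It fixes a compulsory class and a rule for admitting anything else, and arm meets neither: it is not an outcome, and convergence is not why it is needed.

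A second reply is that the loss is easily exaggerated. This also stands in part. A reader might infer that every between-arm difference shrinks by about the fraction missing. That holds only when both follow-ups are lost and nothing in the model stands in for arm. Baseline comparisons are unaffected, an observed 6-week value recovers part of the effect, and adherence recorded as zero in TAU recovers about half of the loss for the two active-versus-TAU contrasts. It does little for arm 1 versus arm 2, and nothing if TAU adherence is left blank. The article does not say which applies.

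A third reply is that the article does not say that satisfaction or adherence would be imputed for TAU. True, but it names all secondary outcomes and makes no exception.

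Finally, a reader might infer that a normal imputation model will yield day counts outside 0 to 7 that the count models cannot use. That is implementation detail. Its size would rest on an assumed mean and SD, the package can bound values, and the count distributions are given only as examples.

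**Conclusion.** The point holds in conditional form. The variable list does not name the arm that the analysis compares, and it takes in two measures that have no meaning in TAU before 3 months. If it is followed as written, a true 3-month difference of 0.30 SD would be estimated at about 0.24-0.26, 0.20-0.23 or 0.15-0.21 with 20%, one third or half of the 3-month values missing. The lower end applies when the 6-week value is always missing too, and the upper end when it is always observed. The loss is smaller for active versus TAU if adherence is recorded as zero in TAU. With arm in the model there is no material shrinkage.

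The bias is towards no difference, so the cost is power and an understated effect, not false positives. The figures rest on the assumed correlation of 0.5, equal effects at both follow-ups, missingness at random and the assumed missing rates. The article gives no dropout rate, only the expectation that it will be high.

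**What to change.** Add to the Data Analyses section that study arm is part of the imputation model, either as two indicators with the repeated outcomes in wide format or by running the imputation separately in each arm. State also that program-specific measures (CSQ-I and adherence) are left out of the imputation for TAU.

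Imputing separately by arm meets both requirements at once. If arm indicators are used instead, CSQ-I and adherence need a run restricted to the two active arms, where they are defined.

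If the full protocol or analysis plan already specifies this, the article's sentence only needs to be brought into line with it. The cost is one or two sentences and a few lines of code. Data collection and sample size do not change.

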### Safety

Potential risks are expected to be minimal as no drugs will be administered and the medical device (ie, the self-help tool) was determined to be of very low risk during the course of its European conformity certification. What we expect to observe is some mild withdrawal symptoms such as craving, mild depressive states, and sleep problems. These issues will be addressed in the psycho-educational modules that are part of the 6-week self-help intervention. At all times, an *instant help* Web page will be available with instructions on what subjects can do if their situation becomes unbearable. These instructions contain psycho-educational self-help instructions, as well as phone numbers to professional health care providers.

## Results

The study will be conducted in accordance with the ethics board–approved protocol and the principles stated in the current version of the Declaration of Helsinki; the CONSORT eHealth Guidelines [47] for studies on medical devices; the European Directive on medical devices 93/42/EEC; and the ISO Norm 14155 and ISO 14971 as well as Swiss Law and Swiss Regulatory Authority requirements. The local ethics committee and regulatory authorities will receive annual safety and interim reports and be informed about study termination, in agreement with local requirements.

The study was approved by the ethics committee of the Canton of Zurich on July 4, 2016 (BASEC-Nr. 2016-00264) and is registered at Current Controlled Trials, traceable as ISRCTN11086185.

Results will be published in a scientific peer-reviewed journal. Anonymized study data will be available on request. Participants will be informed via email about study results via a lay-person-friendly summary of trial findings, if they have requested so at registration.

## Discussion

### Principal Findings

To the best of our knowledge, this study will be the first to assess the effectiveness—in terms of increasing adherence and treatment success—of adding a social presence to adherence-focused guidance by implementing a human element, in accordance with the supportive accountability model [25], all within the context of a Web-based self-help intervention program to reduce problematic cannabis consumption. The results of this RCT could add valuable insights into how to increase adherence to Web-based self-help tools, for which high attrition rates are one of the greatest reported problems. If users do not adhere to the created content, treatment success is unlikely. If these relatively simple techniques are shown to increase adherence, these ideas could be extrapolated further and easily applied to both current and future Web-based self-help tools to aid in reducing problematic substance use of any kind.

Although it must be noted that participants in the first CANreduce study who received at least one chat session still performed better than those in the same treatment condition who did not [10], the offer of being able to contact an eCoach who is perceived as benevolent, trustworthy, and having expertise by email, with any questions or problems, might adequately reproduce this beneficial effect.

Although adherence and treatment success have already been shown to be greater in interventions in which participants have the option of speaking with a therapist [10], the complexity and costs are increased as well, as such sessions need to be scheduled, and therapists must be available. Such increases in cost and complexity should not be a problem with the human element that we will be implementing, as it is a one-time effort to shoot the videos and prewrite emails with a personal feel. We expect that these features alone will increase program effectiveness; and furthermore, that very few actual emails will be sent by subjects seeking answers. If more emails than anticipated need to be answered individually, this task could be handled by multiple people to address less complex issues. Meanwhile, the email format itself should leave enough time for us to gather input from experts to address more complex questions.

To explore the possible effects of the added content addressing CMDs, we will compare outcomes against the study that examined the first version of CANreduce. Another avenue for exploration will be measuring adherence with specific modules that address CMDs.

### Limitations

The following protocol limitations must be considered:

First, cannabis users who are currently receiving other treatments to reduce their cannabis consumption will be excluded. However, CANreduce was designed to access cannabis users who—for personal or practical reasons—would not attend traditional addiction counseling. Second, all measurements will be self-reported. Third, most of the self-report instruments we will be using have not been validated in a Web-based context, though they have largely been validated in other research and clinical settings. Fourth, as found in the previous Web-based intervention [10,22], we expect rather high rates of dropouts. Finally, another possible limitation of Web-based studies is the potential for low adherence rate because of the distant nature of intervention.

### Conclusions

This study will evaluate the effectiveness of an enhanced version of CANreduce, a Web-based self-help intervention to reduce problematic cannabis consumption. If shown effective, the importance of CANreduce as a tool by which to reach users in the general population who otherwise would not seek out traditional mental health care, and addiction counseling services will be documented.

The benefits of the intervention include providing cannabis users with a better understanding of their addictive behaviors, teaching them psychological tools to handle drug cravings and prevent relapses, and, ultimately, helping them to become free of cannabis dependence.

Furthermore, if adding a social presence to adherence-focused guidance augments the program’s effectiveness, valuable insights could be gained into how to more effectively design Web-based interventions. These findings could then be adapted to other Web-based self-help tools, which present poor adherence and high attrition rates.

## Abbreviations

ADHD: attention deficit hyperactivity disorder
ASRS-V1.1: ADHD Self-Report Scale-V1.1
CBT: cognitive behavioral therapy
CES-D: Centre of Epidemiologic Studies of Depression Scale
CMD: common mental disorder
CSQ-I: Client Satisfaction Questionnaire adapted to Internet-based interventions
CUDIT-R: Cannabis Use Disorders Identification Test-Revised
DALY: disability-adjusted life year
DSM-IV: Diagnostic and Statistical Manual of Mental Disorders, 4th edition
eHealth: electronic health
FDA: Fragebogen Substanzanamnese
GAD-7: Generalized Anxiety Disorder-7
GLMM: generalized linear mixed model
ISGF: Swiss Research Institute for Public Health and Addiction
IT: information technology
ITT: intention-to-treat
LMM: linear mixed models
MI: motivational interviewing
PI: principle investigator
PTSD: posttraumatic stress disorder
RCT: randomized controlled trial
SDS: Severity of Dependence Scale
TAU: treatment-as-usual
